## Methods

### Objectives

The primary objective of this study is to evaluate the impact of a commercially available, polyherbal dietary supplement on markers of glycemic control among a sample of adults with prediabetes. The secondary objectives are to investigate the effects of this supplement on lipid and inflammatory markers.

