### Research type

A 12-week, randomized, double-blinded, placebo-controlled clinical trial is being conducted to achieve the objectives of this study. The authors hypothesize that GlucoSupreme™ Herbal will improve a variety of validated markers of glycemic control more effectively than placebo. In accordance with previous studies of dietary supplements among prediabetic adults and the interval between measurements of glycemic control in clinical practice, this proof-of-concept and exploratory study is 12 weeks in duration.

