### Sample size

The research team aims for a final sample of 40 participants with prediabetes in this clinical trial. Participants are recruited from within clinical practices, mobile health screenings conducted as part of a separate non-intervention study [106], support groups, and health fairs, with 20 participants allocated to the active group (GlucoSupreme™ Herbal) and 20 participants allocated to the control group (placebo). In order to account for a conservative and higher-than-expected dropout rate of 10%, 44 participants will be enrolled to achieve the target sample size. The sample size of 44 participants was estimated by assuming 80% statistical power, a significance level (alpha) of 0.05 using a two-sided, two-sample, equal variance *t* test, an anticipated difference in group means of 0.91 standard deviations for continuous variables, and 10% attrition. The sizes of these treatment effects are large (i.e., between-group differences will need to be considerable in order for the treatment to demonstrate statistically significant improvements relative to placebo).

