This study will utilize an adaptive sample size re-estimation (SSR) approach [107] where participant enrollment may be extended beyond the originally planned sample size if interim effect size is smaller than anticipated, but still promising, thereby preserving study power. The adaptive SSR technique will include: (1) examination of available unblinded endpoint data by the study statistician after 30 subjects are enrolled, (2) calculation of conditional power (CP), and (3) sample size modification in order to maintain study power, if required, based on pre-defined limits. CP is defined as the power of rejecting the null hypothesis at the end of the trial conditional on the observed data accumulated up to the time of the planned interim analysis. CP estimates will be categorized into one of three “zones”— Favorable, Promising, or Unfavorable. The Favorable zone will be defined as CP ≥ 80%. CPs in the Favorable zone will require no sample size adjustment (*n* = 40). Similarly, CP estimates that fall into the Unfavorable zone (CP < 50%) will require no sample size modifications (*n* = 40). However, if CP falls into the Promising zone (CP between 50 and 79%), the sample size will be recalculated such that CP equals the originally planned statistical power (i.e., 80%), up to a maximum of 66 subjects. This methodology preserves the overall type I error rate, no adjustments to alpha levels or confidence intervals are necessary, and standard statistical tests can be used for data analysis. Should the trial need to utilize adaptive SSR and enroll to the maximum sample size of 66, a difference in group means of 0.74 standard deviations could be detected.

Participants will be withdrawn from the study if they wish to withdraw or experience serious adverse events (SAEs) for any reason. If SAEs are reported, the site physician and principal investigator of the study will be contacted by the study coordinator, the participant will be withdrawn from the study, and a treatment plan will be implemented. Any dropouts will be included in the statistical analysis as intention-to-treat (ITT) using the last value carried forward (LOCF) method. Subsequent analyses will also be conducted on the per-protocol population which fully completes the study in order to determine if there are any discernible differences in these populations for the purposes of more broadly extrapolating the generalizability of results.

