### Outcome measures

Outcome measures include glycemic parameters, lipids, inflammation, and progression to T2D (Table 2). A number of glycemic parameters in addition to fasting blood glucose and HbA_1c_ are measured throughout this study. Because insulin resistance often sets the stage for progression to T2D by placing a high demand on insulin-producing (β) beta-cells during a prediabetic state, we are using the validated HOMA-IR to estimate insulin resistance (calculated as: (Fasting insulin [μU/L] × Fasting blood glucose [nmol/L])/22.5 [109]). Likewise, the validated Quantitative Insulin Sensitivity Check Index **(**QUICKI) measurement to assess insulin sensitivity has also been used extensively, including in herbal dietary supplement clinical trials, and is (calculated as: 1/Log-fasting blood glucose [mg/dL] + Log-fasting insulin [μU/mL]) [109]. Additionally, pancreatic β-cells produce insulin. Thus, participant HOMA-β is being estimated as well (calculated as: (20 × Fasting insulin [μU/L])/(Fasting blood glucose [mmol/L] – 3.5) [109]).

**Table 2 Tab2:** Primary and secondary outcomes

Endpoint events	
Primary outcomes	
Glycemic parameters	Normal range reference
Fasting blood glucose	< 100.9 mg/dL
Glycosylated hemoglobin/HbA_1c_	< 5.7%
Fructosamine	200–285 μmol/L [63]
GlycoMark	~ 180 mg/dL
Fasting insulin	< 25 μU/L
Absence of high HOMA-Insulin Resistance	General US adult population: < 2.73 vs. ≥ 2.73 [63]
Quantitative Insulin Sensitivity Check Index	~ 100% [66]
Pancreatic β-cell function	~ 100% [66]
Secondary outcomes	
Lipid profile	
Total cholesterol	≤ 19 years: < 170 mg/dL; ≥ 20 years: 125–200 mg/dL
Low-density lipoprotein	< 100 mg/dL
High-density lipoprotein	≤ 19 years: > 45 mg/dL; ≥ 20 years men: ≥ 40 mg/dL; ≥ 20 years women: ≥ 50 mg/dL [129]
Triglycerides	< 150 mg/dL [130]
Inflammation	
High-sensitivity C-reactive protein (hs-CRP)	Varies^a^
Progression to type-2 diabetes (T2D) (according to 2016 ADA diagnostic criteria [39, 40])	

*ADA* American Diabetes Association*, HbA*_*1c*_ glycated hemoglobin/HbA1c, *HOMA-IR* homeostatic model of Insulin Resistance, *US* United States

^a^Elevated CRP levels indicate increased risk of T2DM [131] with normal CRP range 0.0–5.0 mg/L [132], while hs-CRP reference values applicable to cardiovascular risk assessment are < 2.0 mg/L [133]

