### Statistical analysis methods

The number of participants screened, randomized, withdrawn early, and completing the study will be tabulated by treatment group and presented in a Consolidated Standards of Reporting Trials (CONSORT)-herbal diagram [122]. Reasons for early withdrawal, if any should occur, will be presented.

Descriptive statistics will be computed for baseline and demographic characteristics and tabulated by treatment group, and may include means, medians, standard deviations, inter-quartile ranges, and percentages, as dictated by the form of each variable. Independent *t* tests will be used for group comparisons (polyherbal dietary supplement group versus control group) on primary and secondary outcomes for each time point. Data transformations may be performed in the event of non-normally distributed data, or the Wilcoxon-Mann-Whitney non-parametric test will be used to assess differences between the means of outcomes between both groups. Fisher’s exact chi-square will be used to assess differences in categorical variables by group, in order to establish whether additional possible influences of dietary intake, broad differences in physical activity, or other demographic differences between study groups may accompany changes in any of the outcomes of interest. The chi-square test will be used for comparing additional endpoint events (e.g., incidence of T2D).

Study outcomes over the 12-week supplementation period will be analyzed using a mixed-model analysis of variance for continuous variables, which controls for within-subject and between-subject correlation. Repeated measures analysis of variance and logistic regression will be used to evaluate potential changes in physical activity and dietary intake, in order to determine whether these differ by treatment group to potentially influence observed effects of the intervention. If applicable, the proportion of subjects reporting at least one AE will be tabulated in each treatment group and compared using Fisher’s exact test. Statistical significance will be set at *p* < 0.05. No adjustments for multiplicity will be performed. The primary analysis will be conducted on the ITT population. Per-protocol and sensitivity analysis may be conducted as appropriate.

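### Eight primary outcomes are tested at 0.05 without adjustment and with no lead outcome or success rule, and the power calculation and interim extension rule are tied to none of them

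*Protocol article*

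**What the plan says.** The primary objective is to "evaluate the impact of a commercially available, polyherbal dietary supplement on markers of glycemic control among a sample of adults with prediabetes", with markers in the plural. Table 2, titled "Primary and secondary outcomes", puts eight under the primary heading: fasting glucose, HbA1c, fructosamine, GlycoMark, fasting insulin, HOMA-IR, QUICKI and beta-cell function (HOMA-beta). Statistical analysis methods applies t tests to primary and secondary outcomes at each time point, sets the threshold at p < 0.05, and adds "No adjustments for multiplicity will be performed".

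Sample size gives one calculation, "assuming 80% statistical power, a significance level (alpha) of 0.05 using a two-sided, two-sample, equal variance" t test, with "an anticipated difference in group means of 0.91 standard deviations for continuous variables". No variable is named. The same section describes an unblinded look after 30 enrolments. It uses one conditional power (CP), sorted into three zones, and allows extension to at most 66 if CP lies between 50 and 79%. It then says "This methodology preserves the overall type I error rate, no adjustments to alpha levels or confidence intervals are necessary".

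Research type describes the work in these terms: "this proof-of-concept and exploratory study is 12 weeks in duration". It also states the hypothesis that the product will improve a range of glycemic markers more than placebo.

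**The concern.** With eight outcomes of equal rank, an unadjusted threshold and no success rule, nothing in the text stops the trial from being read as positive on whichever marker passes 0.05. The interim rule has the same gap. It needs one CP, the list yields eight, and the person computing it sees unblinded data. Unless a marker is fixed beforehand, it can be chosen once the interim effects are known. At stake are how a single significant marker may be interpreted and whether the decision to extend is truly pre-specified.

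The list also overlaps. HOMA-IR, QUICKI and HOMA-beta are all calculated from fasting glucose and fasting insulin, so several apparent successes can be one result.

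**Working it through.** **1. The plan's own figures.** Two-sided two-sample t test, alpha 0.05, difference 0.91 SD, power 80%: the noncentral t gives 19.96 per arm, so 20, with power 80.1%. This matches 40 completers. For the maximum of 66, about 10% loss leaves 30 per arm and a detectable difference of 0.736 SD, matching the stated 0.74. These are sound single-endpoint calculations.

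**2. Re-estimation alone, one endpoint.** Simulating the zone rule with a conventional final test (maximum 60 or 66, interim at 15 to 30 of 40) gave a two-sided type I error of 4.8–5.0%. The type I error sentence therefore holds for one endpoint.

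**3. Any-of-eight false positive.** With independent tests, 1 − 0.95^8 = 0.337. This is only an upper reference value. Eight simulated t tests with 20 per arm and a common correlation gave:

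| Common correlation | At least one p < 0.05 |
|---|---|
| 0.3 | 29.8% |
| 0.5 | 25.0% |
| 0.7 | 19.5% |
| 0.8 | 16.0% |
| 0.9 | 12.1% |

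A more realistic version computes HOMA-IR, QUICKI and HOMA-beta from simulated glucose and insulin. The article gives neither variability nor correlations. The assumptions are coefficients of variation of 8% (glucose) and 50% (insulin), glucose–insulin correlation 0 to 0.5, and analysis on the raw or log scale:

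| Correlation among measured markers | At least one p < 0.05 |
|---|---|
| 0 | 24.0–25.5% |
| 0.3 | 22.8–24.4% |
| 0.5 | 20.4–22.7% |
| 0.7 | 18.2–20.0% |

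The working range is thus about 18–26%. It counts significance in either direction, to match the two-sided 0.05.

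**4. HOMA-IR and QUICKI.** In conventional units (glucose G in mg/dL, insulin I in μU/mL), HOMA-IR = I × (G/18)/22.5 = I × G/405. QUICKI = 1/(log G + log I) = 1/log10(405 × HOMA-IR). For G = 106 and I = 11, both routes give 0.326. As continuous measures they carry the same information.

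**5. Interim rule under no effect.** The article does not say which effect CP assumes for the remaining data, so the observed trend is assumed. With interim statistic z, n participants' data and N = 40:

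CP = Φ[(z·N/√n − 1.96√N)/√(N − n)]

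- For n = 30, CP = 50% at z = 1.96 × √(30/40) = 1.697, and CP = 80% at z = (1.96√40 + 0.842√10) × √30/40 = 2.062. The chance that one named marker has |z| between these is 2 × [Φ(2.062) − Φ(1.697)] = 5.0%.
- For n = 20, the limits are 1.386 and 1.807, and the chance is 9.5%.

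If any of the eight markers may trigger extension, with the derived indices built as in step 3, the chance is about 24–29% at n = 30 and 40–48% at n = 20. The smaller n matters because the look comes after 30 are enrolled and uses whatever endpoint data are available. Trends in either direction are counted.

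**6. Price of the alternatives.** Bonferroni over eight uses 0.05/8 = 0.00625. Power at 0.91 SD with 20 per arm falls from 80.1% to 50.1%. Restoring 80% needs 33 per arm: 66 evaluable, 66/0.9 = 73.3, so 74 enrolled. One named outcome leaves alpha at 0.05 and the 40/44 sample size unchanged.

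**The case against.** The strongest defence is that the study calls itself exploratory, discloses the absence of adjustment, and says in its Discussion that larger trials should follow any benefit. Unadjusted testing is a common and legitimate choice for such work. This stands, and it lowers the weight of the point. It does not remove it, because the same article states an efficacy hypothesis, powers at 80% and runs a formal interim rule. The label does not say which marker those refer to.

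Three stronger readings are tempting, and the article supports none of them.

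- **A contradiction between two statements.** A reader might set "This methodology preserves the overall type I error rate, no adjustments to alpha levels or confidence intervals are necessary" against "No adjustments for multiplicity will be performed". The methodology meant in the first is the sample size re-estimation just described. It makes no claim about eight endpoints, and step 2 finds it about right for one.
- **34% as the trial's error rate.** That needs eight independent outcomes, which is impossible when three are computed from two others.
- **Any-of-eight as the plan's rule.** The article does not say that one significant marker suffices, or that any promising marker triggers extension. The percentages are conditional on those readings. Extension under no effect is also not itself a false positive.

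It is also fair to say that a full protocol or SAP may name the marker that drives CP. But the article itself fixes eight outcomes as primary and rules out adjustment, and the choice of a lead outcome belongs at protocol level. Finally, the 0.91 SD is given for continuous variables generally, so it can be read as a per-comparison figure. Table 2 shows HOMA-IR as a threshold at 2.73, and if that dichotomy is what is analysed, the identity with QUICKI is no longer exact.

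**Conclusion.** The point holds with moderate weight. Eight unadjusted primary outcomes have no lead outcome and no success rule. If any one counted as success, the false-positive chance would be roughly 18–26% under the assumptions in step 3, and about 12–16% if all eight shared a correlation of 0.8–0.9. All of these are well above 5%. If any promising marker could extend enrolment, that would happen under no effect in about 24–29% of trials with 30 participants' data (40–48% with 20), against about 5% (9.5%) for one named marker.

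The sample size arithmetic and the type I error statement are sound for a single endpoint. What is missing is the endpoint to which they apply. Given the declared exploratory purpose, this should be corrected before the interim look, but it does not undermine the trial.

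**What to change.** Before the unblinded interim look, name one lead primary outcome by amendment; which one is the investigators' choice. State that the 0.91 SD, the 80% power, the conditional-power rule, alpha 0.05 and the type I error statement refer to that outcome alone. Report the other seven as secondary or exploratory estimates with confidence intervals and no confirmatory claim. Where HOMA-IR and QUICKI are both analysed as continuous, do not count them as two independent findings.

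The cost is an IRB amendment and a registry update while recruitment is under way, with a reason given for the change in outcome status. Seven markers lose an unadjusted primary claim. The sample size does not change. Timing matters: a choice made after the unblinded data have been seen would not be credible as pre-specification.

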### Document conservation and summary

Data to be included in this study includes, but is not limited to, demographic information, medical history, current medication(s), study compliance, study outcomes listed previously, AEs, participant withdrawals, and a screener to detect overall changes in dietary behavior and physical activity. After electronic data entry, all data is stored on secure University of Maryland School of Medicine (UMSOM) servers. All study and source documents, including clinic agreements, consent forms, and signatures of study participants, will be retained by researchers for a period of at least 6 years post study completion in a secure place [116]. Only approved study staff will have access to the data.

### Trial management

#### Management of protocols

All study personnel are trained to provide consistent dissemination of study materials and information to participants, and have undergone recent CITI training for Clinical Research (https://about.citiprogram.org/en/homepage/). All researchers, physicians, and related personnel are required to understand and adhere to protocol details and each must have the capability to explain the study process to anyone, including participants. Any changes in protocol will be subject to additional IRB amendment approval.

#### Measures for compliance of participants

Participant compliance is tracked and examined by researchers. The research team verifies that participants have received the study supplement within the predetermined window of time, explains the proper dosage at baseline, and ensures that participants are consuming the expected number of capsules at their 6-week telephone call or visit. The daily diary is checked by researchers at the end of a participant’s duration in the study in addition to pill counts to determine adherence to the study supplement.

#### Monitoring and inspection

Participant data is entered into an Excel spreadsheet within one week of being collected, and is assessed for integrity and consistency by members of the research team in the following order: the study coordinator, the principal investigator of the study, and statistical sub-investigators for the study. The Standard Protocol Items: Recommendations for Interventional Trials (SPIRIT) Checklist is available in Additional file 1.

#### Bias control

All dietary supplements and medications taken by participants during the study period are recorded and analyzed at the conclusion of the study. The daily use of oral hypoglycemic medications or insulin injections during the study period is considered an exclusion criterion during screening and prohibited during the study, resulting in exclusion from the per-protocol analysis, should it occur. Broad changes in dietary intake and physical activity are recorded at each time point in order to account for potential bias.

## Discussion

Over 50% of American adults take a dietary supplement for a variety of health-related goals [123]. Glycemic control is a common goal of dietary supplementation, since prediabetes is an increasingly common risk factor for T2D and pharmacological agents are currently limited in the treatment of prediabetes. There is a pressing need to provide evidence-based options to improve glycemic control so as to prevent the burden of T2D, for which costs have increased 41% between 2007 and 2012 in the United States [124]. The Diabetes Prevention Lifestyle Change Program (DPP) delayed T2D incidence in a multicenter randomized controlled trial in the United States. by 58% compared to metformin (31%) over a 4-year period [125]. Further, 15-year follow-up demonstrated DPP participants continued to delay the T2D development by 27% compared to placebo, superior to metformin (18% delay) [126]. Additional beneficial approaches to delay or prevent T2D are needed for people unable to implement broad lifestyle interventions, such as the DPP, or to perhaps supplement these lifestyle changes. Rigorous evaluation of the safety and efficacy of commercially available, polyherbal dietary supplements appears warranted, as these supplements are popular and may be more representative of traditional and modern herbal medicine practice than single herbs in isolation [82, 127]. In light of the evidence supporting the use of some herbal dietary supplement formulations to improve glycemic parameters, the study investigators hypothesize that the polyherbal dietary supplement under study may restore glycemic parameters to normal ranges, irrespective of broad changes in diet or physical activity. Thus, this polyherbal formulation may ultimately be helpful in deterring the incidence of T2D by preventing glycemic parameters from reaching ranges associated with this costly disease. The randomized, double-blinded design is utilized in this study to gain an understanding of the safety and efficacy of this polyherbal dietary supplement on 12-week changes in short-term, medium-term, and comparatively longer-term markers of glycemic function, as measured by validated laboratory assessment of fasting blood glucose and fasting insulin (short-term), fructosamine (medium-term), and HbA_1c_ (longer-term). In addition, we measure a number of clinically relevant outcomes that capture peak glycemic dysfunction (GlycoMark), insulin resistance, β-cell function, insulin sensitivity (QUICKI), lipid profile (total cholesterol, low-density lipoprotein (LDL), HDL, and triglycerides), inflammation (high-sensitivity C-reactive protein (hs-CRP)), and progression to T2D.

Although the study design is optimized by the selection of a study treatment containing only plant ingredients with demonstrated mechanisms of action (i.e., enzymatic, signal enhancement, etc.) [40, 43, 44, 62–92, 128], the generalizability of this study cannot be extended to smokers since they were excluded for potential safety concerns. In addition, the small sample size of this proof-of-concept and exploratory study confers a limited scope to examine potential adverse effects, and the possibility remains that investigators may find smaller than anticipated effects regarding outcomes. This may pose a potential limitation in drawing conclusions regarding outcomes. However, the study is designed to detect considerable between-group differences, determined a priori through power analyses and the accommodation of an optional use of adaptive sample size re-estimation. If the planned trial shows beneficial effects on the outcomes, subsequent trials should ideally utilize a larger sample and examine potential longer-term (> 12-week) effects of the study treatment on glycemic control.

